#### Quality of life assessment (at baseline and week 6)

Quality of life will be assessed using the World Health Organization Quality of Life Brief Version (WHOQOL-BREF) questionnaire validated in Persian [35]. WHOQOL-BREF is a 26-item self-report scale that evaluates four domains of quality of life including physical, social, psychological, and environmental. Each item is scored one to five according to the Likert scale. The total score for each domain will be reported based on a 0 to 100 scale, and the higher the score, the better quality of life [36, 37].

#### Three-day food and drink diary (at week 1, 3 and 6)

To evaluate the individual’s calorie intake and compliance with the study protocol, participants will be asked to keep a detailed food and drink diary, at weeks 1, 3, and 6.

The subjects will be instructed to meticulously record every item they eat or drink, including the time of ingestion, portion sizes, cooking methods, and any additions like sauces. Participants will be required to document their intake for three consecutive days, including 1 day on a weekend. To ensure accuracy and prevent forgetting or underestimating their intake, participants will be asked to take quick notes using a paper diary. Throughout the study, researchers will be available to address any questions participants may encounter, review the diaries, and clarify any ambiguities or missing data during the follow-up visits.

### Expected outcomes

It is expected that arterial compliance will improve in the TRE group compared to the control group. In relation to secondary outcome measurements, an improvement in lipid profile, liver enzyme tests, FBG, insulin concentration, and insulin resistance is expected. There might also be improvements in cognitive outcomes, a reduction in the hs-CRP inflammatory marker, and changes in body weight and composition, with the latter possibly leading to small changes in RMR.

### Plans to promote participant retention and complete follow-up {18b}

Participants in the TRE group will receive daily messages to improve compliance, while all participants will be contacted and reminded of their scheduled visits.

### Data management {19}

In the current study, the database will be generated by entering data in the SPSS software version 20. To increase the accuracy of data collection, all data will be collected by the primary investigator. To ensure that the information collected during the study is kept securely and confidentially, each participant will be assigned a code that will be used to identify him throughout the study. Two separate, password-protected databases will be created, one containing the participants’ personal information (to which only the primary investigator will have access) and one containing the coded study data (to which the study team will have access). The written information, e.g., consent forms and any other data input forms will be kept in a locked cupboard in the primary investigator’s office. The final dataset will comprise all data collected on each participant identified using their unique code. Data sharing between investigators through networks will also be password-protected and access will be allowed only by investigators with a link sent by the primary investigator. All passwords will be changed every 3 months for security reasons.

### Confidentiality {27}

As explained in the “Data management” section, to ensure the confidentiality of data, each participant will be assigned a code throughout the study, and the databases will be password-protected. Accessing data will be allowed only by other investigators with a link sent by the primary investigator. All passwords will be changed every 3 months for security reasons. No participants will be identified in any publication or other dissemination activities and participants will be free to withdraw from the study without providing any reason and without their care by our team or other healthcare professionals being affected in any way. Collected data, of any kind, will be destroyed 5 years after completion of the study.

### Plans for collection, laboratory evaluation, and storage of biological specimens for genetic or molecular analysis in this trial/future use {33}

Blood samples will be collected from the median cubital vein at each visit. The samples will be centrifuged, and the resulting serum and plasma will be stored at – 80 °C until analysis [38]. Also, the remaining samples will be stored at − 80 °C, at Mashhad University of Medical Sciences for future use.

## Statistical methods

### Statistical methods for primary and secondary outcomes {20a}

The SPSS software version 20 will be used for data analysis based on the intention-to-treat method. Comparison between groups will be conducted by independent sample *t*-test and Mann-Whitney tests for quantitative data, while within-group comparisons will be assessed using paired sample *t*-test and Wilcoxon signed-rank tests. Comparison between groups will be conducted by chi-square test for qualitative data, and within-group comparisons will be assessed by McNemar’s test. Qualitative data (levels of physical activity based on IPAQ) will be presented using frequencies and percentages, while quantitative data (anthropometric parameters, arterial stiffness indices, indirect calorimetry parameters, laboratory tests, appetite VAS score, GNG score, WCST score, WHOQOL-BREF score, PSQI score, pedometer reports, 3-day food and drink diary reports) will be presented using mean and standard deviation or median and interquartile range depending on the data distribution. The relationship between outcomes will be assessed using Pearson’s correlation coefficient and Spearman’s rank correlation coefficient. A *p*-value of < 0.05 will be considered statistically significant.

To mitigate the risk of contamination in TRE trials, we will conduct sensitivity analyses to assess the impact of potential adjustments in the control group’s eating times. Furthermore, we will compare the results of the intention-to-treat analysis with per-protocol analyses, by checking the consistency of these results. Also, appropriate statistical methods will be employed to predict potential contamination and its impact on the study results.

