### Sample size {14}

The sample size was calculated according to the percentage of PWV change in the study by Sutton et al. [13]. Considering an alpha error of 5%, beta error of 20%, and an effect size of 0.63, a sample size of 20 was estimated for each of the two study groups.$$n=\frac{{{\left({z}_{1-^{\alpha }\!\left/ \!_{2}\right.}+{z}_{1-\beta }\right)}^{2}(\sigma }_{1}^{2}+{\sigma }_{2}^{2})}{{\left({\mu }_{1}-{\mu }_{2}\right)}^{2}}$$$$n=\frac{{\left({Z}_{1-^{\alpha }\!\left/ \!_{2}\right.}+{Z}_{1-\beta }\right)}^{2}}{{f}^{2}}$$

Taking into account a 20% loss to follow-up, 24 participants will be enrolled in each group.

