## Data collection and management

### Plans for assessment and collection of outcomes {18a}

Measurements will be conducted at baseline, week 3, and at the end of the intervention (week 6). All assessments will be conducted in the morning, following at least a 10-h fasting period. Before the visits, participants will be informed of the conditions required for the assessments and asked to comply with them.

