### Methods in analysis to handle protocol non-adherence and any statistical methods to handle missing data {20c}

The trial will use an intention-to-treat analysis protocol, to minimize the impact of participant dropouts and non-adherence to the protocol by analyzing all participants according to their original assignment, regardless of whether they completed the study or not. However, missing data from participants who drop out or do not adhere to the protocol will be imputed using statistical methods to ensure that the analysis will not be biased by missing data.

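### PWV and the other quantitative outcomes are compared with unadjusted two-sample tests although baseline and week-3 PWV are measured; the test is valid, but adjusting for baseline is more efficient at almost no cost.

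*Protocol article*

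**What the plan says.** All references are to the Protocol article.

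- **Between arms.** Statistical methods {20a}: "Comparison between groups will be conducted by independent sample" t-test, or by "Mann-Whitney tests for quantitative data, while within-group comparisons will be assessed using paired sample" t-tests and Wilcoxon signed-rank tests. The same section lists arterial stiffness indices among the quantitative data. It names no baseline covariate, ANCOVA or repeated-measures model, and neither does any other section.
- **Visits.** Plans for assessment {18a}: "Measurements will be conducted at baseline, week 3, and at the end of the intervention (week 6". Table 1 and the section on arterial compliance confirm PWV at all three.
- **What is compared.** The abstract defines the primary outcome as changes in PWV, and Sample size {14} is built on percentage change in PWV. Section {20a} does not say whether the tested value is the change or the week-6 value, or how week 3 enters.
- **Size and allocation.** Sample size {14}: "an effect size of 0.63, a sample size of 20 was estimated for each of the two study groups", raised to 24 for dropout. The abstract specifies simple randomisation.
- **Missing data.** Section {20c} commits to analysing everyone as assigned, whether or not they completed. Missing values "will be imputed using statistical methods to ensure that the analysis will not be biased by missing data".

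**The concern.** The trial is small, and each man has a baseline PWV that carries information about his week-6 value. A two-sample test on change uses that baseline with a fixed weight of one. ANCOVA estimates the weight from the data, which lowers the variance whenever r is below 1.

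The estimate is also exposed to chance imbalance. No stratification is described, and a trial of this size can easily produce arms that differ at baseline. A change score then moves the estimate opposite to the imbalance, because high values regress towards the mean. A week-6 comparison moves it in the same direction as the imbalance. Baseline adjustment removes both shifts.

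The planned paired tests within each arm add a risk of misreading. Both arms receive healthy-eating guidelines and nutritionist consultations, so both may improve. A significant change in one arm only would not show that the arms differ.

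**Working it through.** **Inputs.** From {14}: "Considering an alpha error of 5%, beta error of 20%, and an effect size of 0.63", two-sided (its formula uses z at 1 − α/2), 20 per arm before dropout. The baseline-to-week-6 correlation r is assumed, because the protocol gives neither a correlation nor an SD. Range shown: 0.3 to 0.9. Variances at the two visits are taken as equal (s²), and the planned effect is read on the change-score SD.

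**1. The plan's own figure.**
n = (1.960 + 0.842)² / 0.63² = 7.849 / 0.3969 = 19.78, so 20 per arm. This reproduces. In the printed formulas f² = (μ1 − μ2)² / (σ1² + σ2²). With equal SDs the standardised difference is therefore d = 0.63 × √2 = 0.891.

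**2. Relative variance.**
- Change score: 2(1 − r)s²
- ANCOVA: (1 − r²)s²
- Ratio: (1 − r²) / [2(1 − r)] = (1 + r)/2

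**3. Power at 20 per arm** (noncentral t; 38 df for the t-tests, 37 for ANCOVA). The effective d is 0.891 for change, 0.891/√[(1 + r)/2] for ANCOVA and 0.891 × √[2(1 − r)] for week 6 alone.

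| Assumed r | (1 + r)/2 | t-test on change | ANCOVA | t-test on week 6 only |
|---|---|---|---|---|
| 0.3 | 0.65 | 78.4% | 92.5% | 90.1% |
| 0.5 | 0.75 | 78.4% | 88.6% | 78.4% |
| 0.7 | 0.85 | 78.4% | 84.5% | 56.6% |
| 0.8 | 0.90 | 78.4% | 82.4% | 41.2% |
| 0.9 | 0.95 | 78.4% | 80.4% | 23.3% |

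The exact 78.4% is slightly below the planned 80% because the protocol's formula uses the normal approximation, which gives 80.4% at n = 20.

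**4. Chance imbalance.** With 24 per arm the SE of the standardised baseline difference is √(2/24) = 0.289. A difference above 0.3 SD in either direction (0.3/0.289 = 1.04 SE) arises in about 30% of trials, and one above 0.5 SD in about 8%. Given a 0.3 SD imbalance and r = 0.7, the change-score estimate shifts by (1 − 0.7) × 0.3 = 0.09 SD in the opposite direction. A week-6 comparison shifts by 0.7 × 0.3 = 0.21 SD in the same direction.

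**5. Within-arm tests.** Suppose both arms truly improve by the same amount, with 20 per arm. If p is the power of one paired test, TRE significant and control not occurs with probability p(1 − p), which cannot exceed 25%.

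| Common improvement (SD of change) | p | p(1 − p) |
|---|---|---|
| 0.3 | 0.247 | 19% |
| 0.45 | 0.480 | 25% |
| 0.6 | 0.721 | 20% |
| 0.8 | 0.924 | 7% |
| 0.9 | 0.968 | 3% |

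**The case against.** The strongest reply is that nothing here is invalid. Under randomisation a t-test on change is unbiased over repeated trials and keeps its 5% error rate. The imbalance shift is conditional on the imbalance that happens to occur, and at r = 0.7 it is modest. The gain rests on an r that the protocol does not give, and at r = 0.9 it is only 2 points. All of this stands. It limits the size of the point but does not remove it, because ANCOVA is ahead at every r shown.

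Three stronger readings are tempting, and the document does not support them:

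- A reader might infer that the plan ignores baseline. The abstract and {14} both point to change, which does use it. The low week-6-only power figures apply only under a reading that {20a} leaves open but the rest of the article makes less likely.
- A reader might take the 19–25% in step 5 as a false-positive rate. It is the frequency of a pattern at selected effect sizes, and it falls to 3% at 0.9 SD. The protocol plans a between-arm comparison and nowhere says that it will conclude from the paired tests.
- A reader might object that rank tests cannot be pooled after imputation. That presumes multiple imputation of data analysed by rank tests. Section {20c} does not name the imputation method, and {20a} does not assign a rank test to PWV.

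It may also be said that covariates belong in an analysis plan not shown here. But {20a} already names the test for these outcomes, so the point concerns a stated method. Section {20b}, which intends no additional analyses, gives little help either way, since it deals with subgroup and similar analyses.

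**Conclusion.** The point holds as one of efficiency and robustness, not of error: the planned analysis is valid, but it leaves available precision unused. Against a change-score t-test, baseline adjustment raises power at 20 per arm from 78.4% to between 80.4% (r = 0.9) and 92.5% (r = 0.3). It also removes the conditional shift of (1 − r) times any baseline imbalance. These figures assume equal variances at the two visits, the planned effect on the change-score SD, and 20 men per arm with data. If week-6 values alone were tested, the loss would be much larger at high r (56.6% against 84.5% at r = 0.7), which is a reason to state the tested quantity. The within-arm p-values carry a risk of misreading only. The change is well worth making, but the trial's validity does not depend on it.

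**What to change.** In Statistical methods {20a}:

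1. Make the primary analysis the week-6 difference in PWV between arms, adjusted for baseline PWV, with a 95% CI. Use either ANCOVA or a linear mixed model of week-3 and week-6 PWV with arm, visit, arm-by-visit and baseline PWV. The mixed model also uses week-3 values from men who drop out later.
2. Use the same approach for the other quantitative outcomes measured at baseline, transformed if skewed.
3. Report within-arm changes descriptively, without p-values.

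In {20c}, keep imputation for men with no post-baseline value. If plain ANCOVA is chosen, keep it also for men without a week-6 value. Otherwise the adjusted model would drop randomised men whom {20c} commits to analysing.

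The cost is one degree of freedom (about 0.1 power point at r = 0.7: 84.5% with 37 df against 84.6% with 38) and a change of wording. No new data, visits or participants are needed. The article states that no data have yet been analysed, so the change can be fixed in advance.

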### Outcomes {12}

The primary outcome of this trial is to determine the effect of a 10-h TRE compared to standard dietary recommendations on indices of arterial stiffness among men with MetS. The secondary outcomes consist of changes in anthropometric parameters, indirect calorimetry parameters, lipid profile (triglyceride, total cholesterol, LDL, and HDL), liver enzyme tests (AST, ALT, and ALP), FBG and insulin concentrations, insulin resistance (assessed by HOMA-IR) [19], appetite status, cognitive outcomes (assessed by GNG test and WCST), quality of life assessment (WHOQOL-BREF questionnaire), sleep quality (PSQI questionnaire), physical activity assessments (IPAQ and pedometer), and 3-day food and drink diary.

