#### Physical activity assessment (at baseline and week 6)

Physical activity level will be assessed using a pedometer (Omron ri-Axis Pedometer- Step and Activity Tracker HJ-320; Kyoto, Japan) in the first and last 7 days of the study period. The participants’ activity will also be assessed using the International Physical Activity Questionnaire (IPAQ) at the beginning and end of the study. IPAQ includes 5 domains and assesses job-related physical activity, transportation physical activity, housework, house maintenance, and caring for family, recreation, sport, and leisure-time physical activity, and time spent sitting [25, 26]. The validated Persian version of IPAQ will be used [27].

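### IPAQ physical activity, a change outcome, is compared between arms only as levels by chi-square, which discards ordering, within-level change and baseline and costs power on one secondary outcome

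*Protocol article*

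**What the plan says.** The Outcomes section {12} states the secondary outcomes as changes: "The secondary outcomes consist of changes in anthropometric parameters" opens a list that also contains physical activity by IPAQ and by pedometer.

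The section on physical activity assessment schedules the "International Physical Activity Questionnaire (IPAQ) at the beginning and end of the study". It describes an instrument with several components: "IPAQ includes 5 domains and assesses job-related physical activity", followed by other domains that include time spent sitting.

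The Statistical methods section {20a} sorts the variables into two kinds. IPAQ is the only one named as qualitative: "Qualitative data (levels of physical activity based on IPAQ) will be presented using frequencies and percentages". The tests for that kind are: "Comparison between groups will be conducted by chi-square test for qualitative data, and within-group comparisons will be assessed by McNemar’s test". The quantitative list is itemised. It contains the pedometer reports and the sleep, quality-of-life, appetite and cognitive scores, but no IPAQ score and no sitting time. Section {20b} adds that no additional analyses are intended.

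**The concern.** The outcome is a change in activity, but the stated test between the randomised arms is a comparison of level frequencies. Three kinds of information are lost.

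- **Movement inside a level.** A man who becomes more active without crossing a boundary counts as unchanged.
- **Order.** Pearson's chi-square gives the same result however the levels are arranged, so a consistent shift upwards gets no credit for being consistent.
- **Baseline.** A comparison of week-6 levels between arms does not use the value each man had at the start.

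The within-arm test has a separate difficulty. McNemar's test is defined for a paired two-category variable. If IPAQ is scored in more than two levels, the named test does not apply as it stands.

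At stake is the chance of detecting a real difference in IPAQ activity in a trial of 24 men per arm.

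**Working it through.** **The plan's own figure.** The only sample size in the article is for pulse wave velocity. The second formula in Sample size {14} gives n = (1.960 + 0.842)² / 0.63² = 19.78, so 20 per group, and 20 × 1.2 = 24 enrolled. It reproduces. It was not set for IPAQ, and the article gives no power figure for IPAQ.

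**Inputs from the article.** 24 enrolled per arm (20 after the allowed loss), 1:1 allocation, 5% significance; two-sided testing follows from the z(1−α/2) term in the formula.

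**Assumptions, not in the article.** A normally distributed activity score with SD 1 in each arm; three levels cut at ±0.43 SD (tertiles of the control arm); baseline to week-6 correlation 0.6; true shifts of 0.6 or 0.8 SD.

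**Simulation.** Week-6 score = 0.6 × baseline + noise + d × arm, 4,000 trials per setting, 24 per arm:

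| True difference | Chi-square, 3 levels | Mann-Whitney on score | Score adjusted for baseline |
|---|---|---|---|
| 0.8 SD | 53% | 74% | 91% |
| 0.6 SD | 34% | 49% | 71% |

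With two levels cut at the mean, chi-square has 57% power at 0.8 SD. Type I error was about 5% for all three methods on three-level data, so the gaps do not come from a difference in test size.

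**Check by formula at 0.8 SD.**

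- *Level probabilities.* Control: 0.334, 0.333, 0.334. Intervention: Φ(−1.23) = 0.109, then 0.246, then 0.644.
- *Chi-square.* Noncentrality = 24 × Σ(p₁ − p₂)² / (p₁ + p₂) = 24 × (0.1135 + 0.0129 + 0.0987) = 5.40. On 2 degrees of freedom at 5% this gives power 0.54.
- *Score, unadjusted.* 0.8 × √(24/2) = 2.77, and Φ(2.77 − 1.96) = 0.79 for a comparison of means. Mann-Whitney should lie slightly below this.
- *Score, baseline-adjusted.* Residual SD = √(1 − 0.6²) = 0.8, so the standardised difference is 0.8 / 0.8 = 1.0. Then 1.0 × √12 = 3.46, and Φ(3.46 − 1.96) = 0.93. This normal approximation is slightly optimistic.

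The formulas agree with the simulation.

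**Splitting the gap at 0.8 SD.** Categorising costs 74 − 53 = 21 percentage points. Not adjusting for baseline costs a further 91 − 74 = 17 points. Only the first part is specific to IPAQ, because {20a} names no baseline-adjusted model for any outcome.

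**Sensitivity.** A second simulation used 20 per arm, correlations of 0.3, 0.5 and 0.7, and shifts of 0.63 and 0.891 SD. The value 0.891 is 0.63 × √2, the standardised difference implied by the article's formula.

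- At 0.891 SD: chi-square on three levels 0.55 to 0.56; t-test on the week-6 score 0.78 to 0.79; baseline-adjusted score 0.82, 0.87 and 0.97.
- At 0.63 SD: 0.31 to 0.32; 0.49; and 0.52, 0.60 and 0.76.

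Chi-square does not gain as the correlation rises, because it does not use baseline. Across these settings, including no shift, 41% to 59% of men were in the same level at both visits; none of their movement is counted.

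**The case against.** Several points on the other side are sound.

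- **Baseline is used within arms.** A reader might infer that the IPAQ analysis ignores baseline altogether. It does not: McNemar's test pairs baseline with week 6 in each arm. Two separate within-arm p-values do not compare the arms, however, so the point stands for the randomised comparison. The article does not say whether chi-square is applied to week-6 levels or to change of level. The second reading would bring baseline in, but would still lose movement inside a level.
- **The pedometer remains.** Steps in the first and last 7 days are listed as quantitative, so change in activity is not lost to the trial. The pedometer does not fully replace IPAQ: it starts during week 1, whereas IPAQ is the activity measure scheduled for the Day 1 visit, and IPAQ also covers sitting time.
- **Harm to the primary result.** A reader might infer that a weak IPAQ test would falsely support attributing a change in pulse wave velocity to eating time. The article does not say that a null IPAQ result will be used in that way, gives neither arm activity advice in its intervention descriptions, and names sleep quality, not activity, as a confounder in its Discussion. That reading is not supported.
- **McNemar may be valid.** With two levels it applies as written. The number of levels is not stated, so the objection to it is conditional.
- **The power figures are illustrative.** Distribution, cut points and correlation are all assumed, and a self-reported activity score may well be skewed. The percentages would change with other cut points.
- **Detail left to a fuller document.** Scoring rules for IPAQ may well be in the full protocol or analysis plan, and their absence here is no fault. But the article does more than stay silent. It assigns IPAQ to the qualitative class, names the tests and leaves IPAQ out of an itemised quantitative list. That is a stated choice and can be judged as one.

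**Conclusion.** The point holds in a limited form. For a secondary outcome defined as change, the stated between-arm test uses neither the order of the IPAQ levels nor change within them, and on its ordinary reading it does not use baseline. The cost is power: about 21 percentage points from categorising at a 0.8 SD difference with 24 per arm, and about 17 more from not adjusting for baseline, the second being common to all outcomes in the plan. These sizes rest on the assumed normal score, tertile cuts and correlation of 0.6. The ordering of the methods was the same at every correlation and shift examined.

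One secondary outcome is affected. Pulse wave velocity, the sample size and the pedometer analysis are not. This is a cheap improvement of minor severity.

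**What to change.** In Statistical methods {20a}:

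1. Add the continuous IPAQ total and sitting time to the quantitative outcomes. This step alone recovers the loss due to categorising, using tests the section already names.
2. Compare the arms on the week-6 value with the baseline IPAQ value as covariate, on a log or rank scale if the score is skewed.
3. Keep the IPAQ levels, with frequencies and percentages, as description.
4. If levels are still to be tested within arms, state how many there are. With more than two, replace McNemar's test by a marginal-homogeneity or Bowker test.

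The cost is wording only: the values come from the questionnaire already scheduled at baseline and week 6, and no visit or measurement is added. The small downside is that a skewed score needs a transformation or a rank-based model, which is best fixed before the data are seen.

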## Trial design {8}

This study is designed as a randomized controlled trial (RCT), with parallel groups and an allocation ratio of 1:1, in a superiority design framework. Regarding the allocation of each participant to the control and intervention groups, randomization will be run using computerized random number generation and sealed envelopes will be used to conceal the random allocation. The potential participants will be identified among the population of the PERSIAN Cohort Study in Mashhad University of Medical Sciences and will be recruited through phone calls. Screening, including both physical and laboratory examinations, will be carried out to assess the presence of MetS based on IDF criteria [16]. The study design and planned assessments for each stage of the study are explained in detail, in the following sections, and briefly summarized in Table 1. The study protocol adheres to the checklist of the Standard Protocol Items: Recommendations for Interventional Trials (SPIRIT) guidance (Table 1).

**Table 1 Tab1:** The timeline for the enrollment, intervention, and assessment schedule

	**Timepoint**	**Timeline**				
		**Enrollment**	**Allocation**	**Study period**		
				**Day 1**	**Week 3**	**Week 6**
	**Enrollment**	✔				
	**Eligibility screening**	✔				
	**Informed consent**		✔			
	**Allocation**		✔			

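### Correlations between outcomes take no account of arm: if the arms are pooled on week-6 or change values, two outcomes that both respond to TRE can correlate through the treatment effect alone

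*Protocol article*

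**What the plan says.** In the protocol article, under Statistical methods for primary and secondary outcomes {20a}, the whole provision for associations is: "The relationship between outcomes will be assessed using Pearson’s correlation coefficient and Spearman’s rank correlation coefficient". The next sentence sets the threshold for significance at a p-value "of < 0.05 will be considered statistically significant". The article does not say whether the arms are pooled, separated or adjusted for, or whether baseline, week-6 or change values enter.

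The same paragraph does state the role of group for its other tests. It names the independent-sample procedures as comparisons between groups, and for the paired procedures it says "within-group comparisons will be assessed using paired sample" *t*-test or the Wilcoxon test.

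Two other sections matter. Trial design {8} describes a trial "with parallel groups and an allocation ratio of 1:1, in a superiority design framework". Expected outcomes says: "It is expected that arterial compliance will improve in the TRE group compared to the control group". That section also expects improvement in lipids, liver enzymes, fasting glucose, insulin and insulin resistance, and lists body weight and composition among the changes that might occur. Section {20b} plans no additional analyses, so no arm-adjusted version appears elsewhere in the article.

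**The concern.** The usual test of a correlation coefficient treats the data as one homogeneous sample. A two-arm trial is not one sample once treatment has moved the means. If TRE lowers both PWV and insulin, the TRE men sit lower on both and the control men higher on both. The pooled scatter then slopes even if, inside each arm, men with a larger PWV change show no tendency to a larger insulin change.

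A pooled coefficient therefore mixes two questions: whether TRE moved both outcomes, which the between-group tests already address, and whether the outcomes move together among men treated alike. A reader who takes it as the second could see a link between PWV and a metabolic marker that only restates the treatment effect. The risk grows with the effect of TRE.

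**Working it through.** **Inputs from the protocol, Sample size {14}.** The planning assumptions are given as "Considering an alpha error of 5%, beta error of 20%, and an effect size of 0.63". From these the article arrives at 20 men per arm before dropout. The enrolment target follows: "Taking into account a 20% loss to follow-up, 24 participants will be enrolled in each group". Allocation is 1:1.

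**Reproducing the planned size.** The second printed formula gives n = (1.960 + 0.842)² / 0.63² = 7.849 / 0.3969 = 19.78, so 20 per group, as stated. Equating the two printed formulas gives f = difference / √(σ₁² + σ₂²). With equal SDs the standardised difference is therefore d = 0.63 × √2 = 0.891. Reading 0.63 directly as d would need 2 × 7.849 / 0.3969 = 39.55, so 40 per group. The planning effect consistent with 20 per group is thus 0.89 SD, and it applies to PWV only.

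**Induced correlation.** Let two unit-SD outcomes have zero correlation within arms and arm shifts d₁ and d₂. With 1:1 allocation and pooled arms,

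ρ = (d₁d₂/4) / √[(1 + d₁²/4)(1 + d₂²/4)].

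For d₁ = d₂ = 0.891: d²/4 = 0.198, so ρ = 0.198 / 1.198 = 0.17. If either shift is zero, ρ = 0.

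**Rejection rates.** Simulation with normal data, 40,000 trials per case, two-sided 0.05 and zero correlation within arms. The two-sided test and every shift on the second outcome are assumptions. The Monte Carlo standard error at 5% is √(0.05 × 0.95 / 40,000) = 0.1 percentage points.

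| Shift on outcome 1 / outcome 2 (SD) | Induced ρ | Pooled Pearson, 20 per arm | Pooled Pearson, 24 per arm |
|---|---|---|---|
| 0 / 0 | 0 | 4.9% | 5.1% |
| 0.89 / 0 | 0 | 5.1% | 5.0% |
| 0.3 / 0.3 | 0.02 | 5.1% | 5.2% |
| 0.5 / 0.5 | 0.06 | 6.4% | 6.9% |
| 0.63 / 0.63 | 0.09 | 8.5% | 9.6% |
| 0.89 / 0.5 | 0.10 | 9.1% | 10.3% |
| 0.89 / 0.89 | 0.17 | 17.6% | 20.3% |
| 1.2 / 1.2 | 0.27 | 39.2% | 46.7% |

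Pooled Spearman is within about 1.5 points throughout. The Pearson partial correlation given arm, and Pearson within a single arm, reject in 4.8% to 5.2% of trials in every row. A rank-based partial correlation was not simulated. Baseline values correspond to the 0 / 0 row, because randomisation precedes any effect.

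**The reverse error.** Pooling can also hide a real association. Take a within-arm correlation of 0.3 and shifts of 0.89 and −0.89 SD. The pooled ρ is (0.3 − 0.198) / 1.198 = 0.08, and with 20 per arm the pooled test rejects in 6.8% of trials, against 47% for the partial correlation.

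**The case against.** The strongest reply is that pooling is inferred from silence. The labels for between-group and within-group describe independent and paired comparisons, and a correlation is neither, so the missing label proves little. Separate coefficients per arm fit the same sentence and hold 5%. The article is condensed, and an analysis plan not shown may settle the matter. This stands as a limit: pooling is the natural reading of an unqualified sentence, but it is not stated. The point survives because the article does name the statistic and the threshold, and neither named coefficient contains an arm term.

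A second reply is that, if both outcomes shift, the pooled correlation is truly non-zero and rejecting zero is correct. That is right for the pooled quantity. The rejection is false only as a statement about association within arms, and the protocol names no such target and no mechanistic objective.

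A reader might also infer that the planned test will reject because of the treatment effect. The documents do not support that. It requires both outcomes to respond and post-randomisation values to be used. Even at 0.89 SD on both, the pooled test does not reject in about 80% of trials. Nor does the protocol firmly expect weight to change; it says only that it might.

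**Conclusion.** The point holds in conditional form and is minor. As written, the correlation analysis takes no account of arm. If the arms are pooled on week-6 or change values, outcomes unrelated within arms can be declared related because TRE moved both. The inflation is negligible at 0.3 SD on both outcomes and modest at 0.5 to 0.63 SD. It reaches about four times the nominal rate only when the second outcome responds as strongly as the planning effect for PWV. These figures assume normal data, zero within-arm correlation and an effect on the second outcome that the protocol does not supply. The between-group PWV comparison and the sample size are untouched.

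**What to change.** Replace the sentence in {20a} with one to this effect: associations between outcomes will be examined on changes from baseline, by Pearson or rank-based partial correlation adjusted for allocated arm, or separately within each arm, and are exploratory. Add that an unadjusted pooled coefficient will not be read as a relationship among men treated alike.

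No new data are needed. The partial correlation costs one degree of freedom: 37 instead of 38 with 40 men, 45 instead of 46 with 48. With a within-arm correlation of 0.3, no treatment effect and 20 per arm, power is 47% against 48% for the pooled test. Separate coefficients are valid but less precise: a single arm of 20 detects the same correlation in about 26% of trials.
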